## Discussion

The first objective of this research is to study the effectiveness of a patient-customized computerized cognitive training program (GNPT^®^) as a home-based cognitive stimulation tool for stroke patients in the chronic stage of recovery. We hypothesize that training cognitive functions of attention, memory, and executive functions with GNPT^®^ could lead to better function of those cognitive domains post-therapy. Furthermore, we want to study whether customized cognitive training could lead to an improvement in other contexts different from the examination tests, improving performance in both related (near transfer) and unrelated (far transfer) tasks. Finally, we want to study the impact of variables such as demography and etiology on rehabilitation outcome.

The strengths of our study include that it is designed to (1) be easily replicated in new patient cohorts, (2) minimize unintended variability by reducing intervention heterogeneity, (3) adjust the type and difficulty of exercises to the specific cognitive impairment profile of patients, and (4) monitor adherence and performance of each exercise during the whole treatment.

Furthermore, our study focuses on targeting cognitive rehabilitation toward the improvement of the quality of life of the patient. In this sense, we include in our primary outcome measures an assessment of functioning in daily life, before, during, and after the performance of both interventions. Additionally, our design is longitudinal, which offers the possibility of studying the maintenance of the results over time (over 3 and 6 months). The timing of the primary outcome is 3 months. The purpose of the follow-up at 6 months is to check the evolution of patients once they have stopped receiving any type of intervention.

Furthermore, the execution of both interventions will be remotely monitored and we will be able to record the quantity and quality of the execution of the participants. Nevertheless, we consider a limitation the fact that we will not be able to control the environmental conditions in which participants perform the tasks. Another limitation is that the battery assessment will be the same throughout the study, which might create a learning effect and/or ceiling effect in some evaluation tasks.

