CCRS allow adjustment of the type of exercises administered to the specific cognitive impairment profile of each patient, but within a fixed set of possible exercises such that heterogeneity of therapy choice is minimized. This can improve studies by allowing better categorization of patient groups that execute similar training sessions in a similar range of responses [13]. Further, CCRS offers the possibility of applying cognitive rehabilitation at home, while patient adherence and performance can be monitored online, so that patients do not need to live near, lodge near, or travel to a rehabilitation center to receive therapy. Because CCRS therapy is entirely digitized, it generates objective data that can be analyzed to determine the relative effectiveness of these interventions. We hypothesize that by allowing a trained professional to oversee an automated customization program that stratifies the level of difficulty, duration, and stimulus speed of presentation, we will reduce the heterogeneity of traditional cognitive training and improve the efficacy of intervention in chronic stroke patients.

The first objective of this pilot study is to assess if chronic stroke patients with cognitive impairment could benefit from cognitive training through a customized tele-rehabilitation platform (“Guttmann, NeuroPersonalTrainer”^®^, GNPT^*®*^) [14] intended to increase the control of experimental variables (cognitive impairment profile, adherence, and performance) traditionally identified as a source of experimental heterogeneity. The study aims to assess if this benefit could translate into an improvement of the trained cognitive domains (attention, memory, and executive functions).

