### Sample size

This is study will be an explorative pilot study. The total sample size required for a two-arm trial following some currently proposed approximation guidelines is between 24 and 70 [21]. Some recently published studies similar to this one have used sample sizes within this range [22–24]. The aim is to recruit 40 participants (*n* = 20 per group). The results of this pilot study will be used to compute sample size and conduct a power calculation to plan a full-scale study.

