#### Statistical analysis

##### Analysis

Data analysis will be based on the intention-to-treat principle, which means that all participants who were randomized will be included in the final analysis, regardless of their adherence to any of the interventions. To avoid the problems derived from missing data (no attendance to neuropsychological assessments), blank spots will be filled with missing data imputation technique last value carried forward.

In order to detect changes in the variables recorded for the primary outcome and secondary outcome, a within-subject comparison pre-/post-intervention in both groups after both interventions will be made, as well as comparisons between groups (group A and group B).

Our null hypothesis is that a difference between baseline scores (A1 for group A and A3 for group B) and scores post-treatment (A2 for group A and A4 for group B) will not be significantly different from zero. Therefore, the Kolmogorov–Smirnov test will be used to examine the data for normality, and either ANOVA (parametric test) or Kruskal–Wallis (non-parametric test) will be used to analyze the measurements. A significance level of 95% will be used (*P* < 0.05 cutoff). Demographic (age, sex, years of education) and etiologic characteristics (ischemic stroke or hemorrhage) will be described using descriptive statistics for each group (group A and group B). The Bonferroni method will be applied to adjust the overall level of significance for multiple outcomes.

Alternatively, composite indices will be created by transforming raw neuropsychological test scores into z scores using published normative data. Domains will be created by averaging the z scores for each test within the domain (M = 0; SD = 1). This system has been used before in similar studies [44, 45].

If the sample size of this pilot study allows, a longitudinal mixed model will be applied.

Data analysis will be performed by an analyst outside the study with the statistical analysis software R and appropriate packages (“lmm” and “psych”) [46].

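### The first objective is effectiveness, but N = 40 is a pilot size and the stated null is zero pre/post change under GNPT alone; the GNPT-minus-sham difference should be the primary result

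*Protocol article*

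**What the plan says.** The Sample size section gives the status of the trial: "This is study will be an explorative pilot study". It takes its number from a rule of thumb ("The total sample size required for a two-arm trial following some currently proposed approximation guidelines is between 24 and 70") and settles on 40, 20 per group, with no effect size, SD or power. It also says what the data are for: "The results of this pilot study will be used to compute sample size and conduct a power calculation to plan a full-scale study".

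The objective is worded differently elsewhere. The Discussion has: "The first objective of this research is to study the effectiveness of a patient-customized computerized cognitive training program". The Background is milder: "The first objective of this pilot study is to assess if chronic stroke patients with cognitive impairment could benefit from cognitive training".

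The Analysis section then sets out significance testing. The null is that the pre/post change under GNPT is zero (A1 to A2 in group A, A3 to A4 in group B). Within-subject pre/post comparisons are planned for both interventions, together with comparisons of group A with group B. On the threshold: "A significance level of 95% will be used", with a P < 0.05 cutoff. On multiplicity: "The Bonferroni method will be applied to adjust the overall level of significance for multiple outcomes". The number of tests is not given. A longitudinal mixed model is to be used only if the pilot's sample size permits.

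**The concern.** Three parts of the article pull apart: the objective asks about effectiveness, the sample size was set for planning a later trial, and the stated null concerns change under one intervention.

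This matters in two ways. First, the stated null does not involve sham. The Discussion admits that repeating the same battery may produce a learning effect, so a GNPT pre/post change can differ from zero without any advantage over sham. Second, a parallel comparison of 20 with 20 under Bonferroni has so little power that a non-significant result would leave a moderate benefit entirely possible.

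The quantity that serves both the objective and the planning purpose is the within-person difference between change under GNPT and change under sham. The crossover yields it, but the Analysis section does not state it as the target.

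**Working it through.** **The plan's own figure.** N = 40 cannot be reproduced by a formula, because no effect size, SD or power is given. The only check is that 40 lies between 24 and 70, which it does.

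**Inputs from the article.** 40 patients, 20 per sequence (Sample size); overall alpha 0.05 with Bonferroni (Analysis); nine named primary measures (Primary outcome measures: 2 attention, 3 memory, 4 executive). The composites are built from performance-based measures only, so three composites plus the three rating scales (RSAB, PRMQ, BRIEF-A) make 6 tests. The composites alone make 3.

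**Assumptions.** Two-sided t tests, 40 completers, no carry-over, and true effects of 0.3 and 0.5 SD. None of these effects comes from the article.

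**Thresholds (38 df).** Alpha per test is 0.05/9 = 0.0056, 0.05/6 = 0.0083 and 0.05/3 = 0.0167. The critical t values are 2.94, 2.78 and 2.51.

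**Group A versus B, 20 per group.** Noncentrality = d × √(20/2). At d = 0.5 this is 1.58; at d = 0.3 it is 0.95.

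**Within-person GNPT minus sham.** For each patient, D = (change under GNPT) − (change under sham). Noncentrality = d × √40, with d in SDs of D. At 0.5 this is 3.16; at 0.3 it is 1.90.

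Power from the noncentral t distribution:

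| Contrast | True effect | 9 tests | 6 tests | 3 tests |
|---|---|---|---|---|
| Group A v B | 0.5 SD | 10% | 13% | 19% |
| Group A v B | 0.3 SD | 3% | 4% | 7% |
| Within-person | 0.5 SD of D | 59% | 65% | 74% |
| Within-person | 0.3 SD of D | 17% | 20% | 29% |

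**Units.** The two contrasts are scaled by different SDs. If the SD of D is √(2(1 − ρ)) times the between-patient SD, where ρ is the correlation between a patient's two values, the scales coincide at ρ = 0.5. For an effect of 0.5 between-patient SD, within-person power is 26%, 31% and 40% (9, 6 and 3 tests) at ρ = 0, and 87%, 90% and 94% at ρ = 0.7. Even at ρ = 0 it is about twice the A versus B figure or more.

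**The stated null.** A pre/post test on 40 patients has the same form, √40 times the change in SDs of the change. Suppose GNPT adds nothing beyond sham and practice alone brings 0.5 SD. The chance of significance on a given measure is then about 59% with 9 tests. An assumed practice gain of 0.3 SD plus a training effect of 0.3 SD makes 0.6 SD, which gives about 80%.

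**Precision.** The 95% CI half-width is 2.02/√40 = 0.32 SD of D within-person, and 2.02 × √(2/20) = 0.64 SD for A versus B. The SD of D, with 38 df, has 95% limits of √(38/56.9) = 0.82 to √(38/22.9) = 1.29 times its estimate, which is usable for planning if the uncertainty is shown.

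**The case against.** The strongest reply is that the article is cautious. It calls itself exploratory, says that patients could benefit and that training could lead to improvement, and gives planning as the use of the results. That stands: the article commits to no definitive claim of efficacy, and nowhere does it say that a non-significant result will be read as no effect.

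Three stronger inferences are tempting, and the article does not support them.

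- A reader might conclude that neither a positive nor a negative result could support anything. That goes too far. A small sample does not spoil a Bonferroni-controlled positive: the family-wise error stays at or below 0.05, against 1 − 0.95⁹ = 0.37 for nine independent unadjusted tests. A crossover contrast at 0.5 SD also has respectable power.
- A reader might expect the written rule to give a non-significant result. The low power figures belong to A versus B and to small within-person effects, not to the stated pre/post null, which practice gain may push towards significance.
- A reader might fault the article for not listing retention or sessions completed as pilot results. A journal article may leave such detail to the full protocol, and this one does say that adherence and execution are monitored.

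It can also be said that the group comparison or the conditional mixed model might in practice deliver the crossover contrast. They might. But the article says neither, and the one hypothesis it does spell out is the single-condition change.

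**Conclusion.** The mismatch holds and should be corrected, though it is not fatal to the trial. The pilot sizing is legitimate for the planning purpose. What does not fit is an effectiveness objective tested through a null that omits sham, with a parallel comparison beside it that has 10% to 19% power at 0.5 SD.

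A positive pre/post result would fail to show benefit over sham because of the choice of null, not because of the sample size. A negative A versus B result would be uninformative because of the sample size. The within-person contrast repairs the first problem and much of the second, although at 0.3 SD of the difference its power is still only 17% to 29%, so estimation is the right frame.

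The power figures rest on assumed effects, full completion and no carry-over. Dropout or carry-over would weaken the within-person contrast. The logical point about the null depends on none of these assumptions.

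**What to change.** 1. In the Analysis section, replace the single-condition null with the within-person GNPT-minus-sham difference in change: (A2 − A1) − (A4 − A3) in group A and the reverse in group B, averaged over the two sequences so that a practice effect tied to period cancels. Make its estimate with a 95% CI, for each domain, the primary result.
2. Label the Bonferroni-adjusted P values exploratory.
3. Report the SD of that difference as the input for the full-scale sample size.
4. In the Background and the Discussion, word the first objective as estimating this difference.

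Keep n = 40. The change uses assessments already planned and needs only wording and analysis effort. Recruitment was still under way when the article was submitted, so at that point it could be made before analysis. The price is that the report cannot claim effectiveness on the strength of a P value.

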## Trial status

This article was submitted on January 3, 2018. Recruitment is ongoing.

## Abbreviations

CPT-II: Conners Continuous Performance Test
A1: first assessment
A2: second assessment
A3: third assessment
A4: fourth assessment
A5: fifth assessment
BRIEF-A: Behavior Rating Inventory of Executive Function–Adult
GNPT^®^: “*Guttmann, NeuroPersonalTrainer”*^*®*^
PMR: Spanish phonemic fluency test
PRMQ: Prospective and Retrospective Memory Questionnaire
RSAB: Rating Scale for Attentional Behavior
TMT: Trail Making Test
WAIS: Wechsler Adult Intelligence Scale
